## Abstract

**Background:**

High-quality neonatal resuscitation (NR) depends on timely execution of technical and nontechnical skills. Simulation-based training improves NR performance, but it is resource-intensive and difficult to deliver at sufficient frequency. Immersive virtual reality (VR) simulation may provide a scalable supplement to traditional mannequin-based training; however, evidence from European neonatal training settings is limited.

**Objective:**

The aim of this study is to evaluate whether immersive VR-based simulation training used as a supplement to traditional mannequin-based simulation training improves NR performance among doctors and nurses in Denmark.

**Methods:**

NEONATAL is a multicenter, individually randomized, 2-arm controlled superiority trial with a parallel-group pretest-posttest design (trial registration number ISRCTN 43822066). Resident doctors and neonatal nurses from 4 hospitals in Eastern Denmark will be randomized to either traditional mannequin-based NR training alone or traditional mannequin-based simulation training supplemented with immersive VR simulation training. Outcomes will be assessed at baseline and endline at 6 to 8 weeks using standardized neonatal simulation scenarios, validated assessment tools, and questionnaires.

**Results:**

The study was funded in July and October 2025, as well as in January 2026. Participant recruitment began in October 2025 and was completed in December 2025, with 66 participants enrolled. Data collection was completed in February 2026. Data cleaning and analysis will take place from March to July 2026, and the results are expected to be published in autumn 2026. This study will provide data on the effectiveness, feasibility, and usability of immersive VR simulation training as a supplement to traditional mannequin-based NR training in routine clinical education.

**Conclusions:**

The NEONATAL study addresses an important gap in NR education by evaluating immersive VR simulation training as a supplement to traditional mannequin-based training.

## Introduction

Neonatal health is a crucial component of global child health. Despite advances in global child health, neonatal mortality remains a major challenge, accounting for nearly 47% of the 4.9 million under-5 deaths recorded globally in 2022 [1,2]. Preventable neonatal morbidity and mortality persist even in high-resource settings, particularly during the first minutes of life, when rapid and coordinated interventions by well-trained health care workers (HCWs) are essential. Up to 85% of newborns breathe spontaneously at birth, approximately 10% of newborns require basic interventions such as drying, warming, stimulation, or airway maneuvers, and around 5% require positive pressure ventilation (PPV) to support breathing. Fewer than 0.3% of newborns need advanced resuscitation, including chest compressions or medication [3].

Global initiatives, including the United Nations’ Sustainable Development Goals, aim to reduce under-5 mortality to at least 25 per 1000 live births and neonatal mortality to 12 per 1000 live births by 2030 [4]. The leading causes of neonatal mortality globally are prematurity, intrapartum-related complications (including birth asphyxia), and neonatal infections, all of which are preventable or treatable with timely, evidence-based care [5,6]. Achieving these outcomes requires HCWs who are not only knowledgeable but also able to translate skills into rapid, coordinated actions during emergencies, which remain a significant challenge [7-10]. In neonatal resuscitation (NR), patient outcomes are highly dependent on the HCWs’ ability to perform time-critical interventions, particularly airway management and initiation of effective PPV [3]. Timely initiation of ventilation is critical, as delaying ventilation by just 30 seconds increases the risk of adverse outcomes, including morbidity and mortality, by 16% [11]. Simulation-based training (eg, using mannequins) has demonstrated effectiveness in improving NR skills, team communication, and outcomes [12,13]. However, traditional training requires physical presence, trained instructors, and structured environments—which limits scalability in busy health care settings. As a result, maintaining proficiency remains challenging because NR events occur relatively infrequently in clinical practice, while technical and decision-making skills may deteriorate without repeated training opportunities.

Immersive virtual reality (VR) provides a potential educational solution. VR allows learners to practice high-pressure clinical scenarios in realistic, repeatable, and engaging environments, without the logistical burden of traditional simulation training. Recent studies demonstrate VR’s potential in health care education to enhance skill performance, knowledge acquisition, and clinical decision-making [14-16]. Using VR in medical training enables the user to be exposed to a highly realistic learning environment, as it combines the view of a real environment with additional virtual content through a screen or a VR headset [17]. Using VR as a teaching and training method can offer multiple advantages [16,18]:

It allows learners to train independently at their own pace and location. No instructor is needed to observe the performance of trainees, and scenarios can be practiced as many times as desired.

It helps train the essential individual components in management and provides interactive features such as voice, sound, and haptic feedback, as well as immediate learner feedback, which supports taking control of the learning process.It is cost-effective and affordable compared to other medical equipment. New training software programs can be updated remotely, and the hardware has a long operational expectancy.

We conducted a feasibility study in Tanzania (2024‐2025), across 3 hospitals with Public Health Laboratory-Ivo de Carneri as the facilitating local partner. The VR prototype was piloted on Meta Quest 3 headsets with 44 participants in clinical settings and showed that frontline HCWs, including doctors and nurses, who completed the pilot NEONATAL VR scenario in NR demonstrated improved clinical skills and high acceptability of the platform.

Despite growing evidence, gaps remain regarding VR’s effectiveness for NR training across different levels of HCWs, including medical doctors, and within European health care systems [17,19-22]. The NEONATAL randomized controlled superiority trial aims to investigate whether immersive VR simulation training, used as a supplement to traditional mannequin-based simulation training in Danish hospitals, improves NR performance. We hypothesize that repeated, deliberate practice under time pressure through immersive VR will enhance adherence to NR guidelines and improve HCWs’ NR performance, including rapid airway assessment, effective PPV, and timely initiation of critical actions.

## Methods

### Aim

The aim of NEONATAL is to study the effectiveness of VR-based simulation training in NR as a supplement to traditional simulation training for improving NR performance among doctors and nurses in Denmark. By the end of the study, we aim to have established a replicable framework that is scalable to other European countries.

The specific research objectives of NEONATAL are as follows:

to investigate whether VR-based simulation training in NR improves clinical skills and serves as an effective supplement to traditional mannequin-based simulation training in 4 Danish hospitals (primary outcome).to investigate whether VR-based simulation training in NR on clinical knowledge is an efficient supplement to traditional mannequin-based simulation training (secondary outcome)to explore HCWs’ cognitive, emotional, and motivational responses during the VR-based simulation training (secondary outcome)to determine the feasibility and usability of VR-based simulation training in routine clinical training settings in Denmark (secondary outcome)

### Study Design

NEONATAL is a multicenter individually randomized, 2-arm, controlled superiority trial with parallel-group pretest-posttest design that was conducted from October 2025 to February 2026. Immersive VR-based simulation training as a supplement to traditional mannequin-based simulation training will be compared to exclusive traditional mannequin-based simulation training. We follow the SPIRIT (Standard Protocol Recommendations for Interventions Trials) guidelines (Checklist 1) [23].

### Study Setting, Population, and Recruitment

The study will be conducted at pediatric departments at 4 hospitals located in Region East, Denmark:

Hillerød Hospital serves as a regional hospital in North Zealand. There are around 4000 births per year, and the hospital has a neonatal department with specialized level 2.Rigshospitalet serves as Denmark’s most highly specialized hospital and receives patients from Denmark, Greenland, and the Faroe Islands. There are around 6000 births per year, and the hospital has a neonatal intensive care unit with specialized level 4.Roskilde Hospital serves as a regional hospital in Region Zealand. There are around 3500 to 4000 births per year, and the hospital has a neonatal department with specialized level 2.Holbæk Hospital serves as a regional hospital in Region Zealand. There are around 1500 births per year, and the hospital has a neonatal department with specialized level 2.

Resident doctors and nurses from any of these hospitals with a clinical role involving neonatal care will be eligible for inclusion.

The inclusion criteria are as follows:

Resident doctors with clinical function in neonatologyNurses with clinical function in neonatology

The exclusion criteria are as follows:

No informed consentChange of workplace (to the nonstudy site) before endline or unable to participate in the study until endlinePreviously attended any formal training with VRNot fully proficient in Danish

Eligible candidates will be contacted by email as well as through informational meetings at the departments and invited to participate in the study. Informed and written consent, along with permission to record and store all video data and voice recordings for the research project, will be obtained from all participants upon enrollment.

Participant recruitment was completed in December 2025.

### Assessment Tools and Outcomes

A comprehensive evaluation strategy will assess clinical skills and clinical knowledge, as well as user experience, including cognitive, emotional, and motivational responses.

#### Primary Outcome

Clinical skills performance and adherence to the 2025 European Resuscitation Council Guidelines for Resuscitation (ERC)—Newborn Life Support (NLS) [24] will be evaluated during scenario execution at baseline and endline using mannequins. The evaluation will be performed by 2 assessors, using structured video observation checklists. The assessors are blinded for participant randomization. The NeoCheck, a validated 38-item checklist developed through a Delphi process, will be used to objectively assess participant performance during the NR simulation [25]. The maximum total score for NeoCheck is 48 points. Moreover, 4 additional global skills in logic and structured management, timing, practical applications, and errors will be rated, with a maximum total score of 8 points, as well as time to critical actions. Therefore, the total maximum score for the primary outcome is 56 points. The baseline and endline NeoCheck assessments are conducted as standardized individual simulation scenarios, in which each participant independently performs NR assessment and management tasks using the same assessment framework and scoring criteria to ensure comparability across assessments.

#### Secondary Outcomes

Clinical knowledge acquisition will be evaluated through preintervention and postintervention tests with multiple-choice questions (MCQs) aligned with the 2025 NLS curriculum [24]. The NEONATAL study group has developed the NR clinical knowledge test specifically for this project. The test consists of 23 MCQs, with 4 options and 1 correct answer.

Cognitive, emotional, and motivational responses will be evaluated at baseline and endline through the following:

NASA Task Load Index (NASA-TLX) is a validated scale measuring perceived workload related to a specific task [26]. The workload score is based on 6 dimensions (mental, physical, and temporal demand, performance, effort, and frustration), and each dimension is scored from 0=very low to 100=very high, in increments of 5. This is based on the participants’ experience during the task. NASA-TLX has previously been forward-backward translated to Danish by 2 professional translators and tested in a Danish context [27].Intrinsic Motivation Inventory (IMI) is a validated questionnaire measuring intrinsic motivation related to a specific activity on a 7-point Likert scale ranging from 1=not at all true to 7=very true [28]. A 7-item version of the scale has recently been forward-backward translated to Danish and tested in a Danish context [27]. It includes the items from the subscale interest/enjoyment and will be used in this study.

The feasibility and usability of VR will be evaluated at endline through the following:

System Usability Scale (SUS) is a validated questionnaire measuring the subjective usability of a product on a 5-point Likert-scale ranging from 1=strongly disagree to 5=strongly agree [29]. The SUS item scores are subsequently converted into a single SUS score on a scale from 0 to 100. SUS has previously been translated professionally to Danish and validated in a Danish context [30].Virtual Reality Sickness Questionnaire is a validated questionnaire measuring motion sickness in a VR environment on a Likert-type scale ranging from 0=none to 3=severe [31]. It includes 9 items covering symptoms of cybersickness.Records of training sessions and adherence, including the number and duration of VR sessions.

Further details regarding the study hypotheses, assessment tools, outcomes, and analysis methods are provided in Table 1.

**Table 1. T1:** Assessment tools, outcomes, and analysis plan.

Outcome	Assessment tool	Participants	Time points	Hypothesis	Analysis method
Primary outcomes					
Clinical skills					
Clinical skills in NR^a^	NeoCheck [25] 38 clinical skills (preparation and resuscitation) 4 global skills Scoring: 0‐3 scale Total points: 56 Video-recorded, dual-rated, raters blinded	All (N=36)	Baseline (t_0_) Endline (t_3_)	Mean change in skills score will be significantly greater in intervention vs control group (superiority hypothesis)	Linear mixed effects model with hospital as a random effect and baseline score as covariate, intention-to-treat analysis
Time to critical actions	Video observation with time-stamping Time from birth to PPV^b^ initiation Time from birth to CPR^c^ initiation Time to scenario completion Right-censored at 900 (time to PPV and CPR) and 1200 seconds (time to complete scenario) if action not performed	All (N=36)	Baseline (t_0_) Endline (t_3_)	Intervention group will have higher hazard of performing critical actions (ie, faster performance) compared to the control group	Cox proportional hazards regression with robust SEs clustered by hospital, baseline time as covariate. Report HR^d^ with 95% CI and *P* value. Kaplan-Meier curves for visualization. Sensitivity analyses: AFT^e^ models with Weibull distribution, logistic regression for action completion (yes/no)
Secondary outcomes					
Clinical knowledge					
Clinical knowledge in NR	NR Knowledge Test 23 MCQs^f^ (4 options, 1 correct) Aligned with ERC^g^ NLS^h^ guidelines [24] Scored as percentage correct	All (N=36)	Baseline (t_0_) Endline (t_3_)	Mean change in knowledge score will be significantly greater in intervention vs control group	Linear mixed effects model with hospital as a random effect and baseline score as covariate
Cognitive, emotional, and motivational responses					
Perceived workload	NASA Task Load Index [26] 6 dimensions: mental, physical, temporal demand, performance, effort, and frustration Scoring: 0‐100 (increments of 5) Danish validated version	Intervention only (N=18)	Baseline postintervention assessment (t_1_) Endline (t_3_)	Exploratory: change in perceived workload from first to final VR^i^ exposure	Paired *t* test or Wilcoxon signed-rank test
Intrinsic motivation	Intrinsic Motivation Inventory [28] 7 items (interest/enjoyment subscale) Scoring: 7-point Likert scale (1=not at all true, 7=very true) Danish translated version	Intervention only (N=18)	Baseline postintervention assessment (t_1_) Endline (t_3_)	Exploratory: change in intrinsic motivation from first to final VR exposure	Paired *t* test or Wilcoxon signed-rank test
Feasibility and usability					
System usability	System Usability Scale [29,30] 10 items about perceived usability Scoring: 5-point Likert scale (1=strongly disagree, 5=strongly agree) Converted to 0‐100 score Danish validated version	Intervention only (N=18)	Endline (t_3_)	Exploratory: descriptive assessment of VR usability (benchmark: score >68=above average/acceptable)	Descriptive statistics (mean, SD, 95% CI)
Cybersickness	Virtual Reality Sickness Questionnaire [31] 9 symptoms of cybersickness Scoring: 0‐3 Likert scale (0=none, 3=severe) Scoring: 0‐100	Intervention only (N=18)	Endline (t_3_)	Exploratory: assess prevalence and severity of VR-related side effects	Descriptive statistics (frequency, mean, SD)
VR training adherence	VR session records Number of sessions completed Total training time	Intervention only (N=18)	Throughout intervention (t_2_)	Exploratory: describe VR training patterns and dose-response relationship	Descriptive statistics; correlation with skill/knowledge gains

a NR: neonatal resuscitation.

b PPV: positive pressure ventilation.

c CPR: cardiopulmonary resuscitation.

d HR: hazard ratio.

e AFT: accelerated failure time.

f MCQ: multiple-choice question.

g ERC: European Resuscitation Council.

h NLS: Newborn Life Support.

i VR: virtual reality.

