### Data Analysis

All quantitative analyses will be conducted using R (R Foundation for Statistical Computing) software and will follow the intention-to-treat principle, with participants analyzed according to the randomized group. Missing data will be explored descriptively and handled using multiple imputation under a missing-at-random assumption, with complete-case analyses conducted as sensitivity analyses. All statistical tests will be 2-sided with *α*=0.05.

Descriptive statistics will summarize baseline characteristics by group, with continuous variables reported as median (IQR) and categorical variables as n/N (%). Prior VR experience and cybersickness scores will be described and explored as potential factors influencing participant engagement and study outcomes.

The primary outcome is NR clinical skills performance, assessed at baseline and endline using standardized checklist scores. All video-recorded scenarios will be independently rated by 2 blinded assessors; interrater reliability will be evaluated using the intraclass correlation coefficient (ICC), with ICC≥0.75 considered acceptable. If ICC <0.75, discrepancies will be resolved through consensus discussion or adjudication by a third rater. Final skill scores will be calculated as the mean of the 2 assessors’ scores unless adjudication is required. Between-group differences in end-line NR skill scores will be analyzed using linear mixed effects models with randomized group as a fixed effect, baseline score as a covariate, and hospital as a random intercept to account for clustering.

Time-to-critical NR actions (eg, time to initiation of PPV or cardiopulmonary resuscitation) will be analyzed using Cox proportional hazards models with hospital-level clustering, applying prespecified minimum clinically important time differences (eg, 30 s for PPV initiation) to support the interpretation of clinical relevance. Secondary continuous outcomes, including knowledge scores, will be analyzed using analogous mixed effects models. Outcomes collected only in the VR group (eg, cognitive workload, motivation, usability, and cybersickness) will be analyzed descriptively and, where measured longitudinally, using within-group comparisons. Given the exploratory nature of the secondary outcomes, we will not adjust for multiple testing, and the results will not be interpreted as confirmatory.

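### Table 1 ranks time to critical actions as primary beside the skills score, other sections have the score as the only primary outcome, and no multiplicity rule applies if Table 1 governs

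*Protocol article*

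**What the plan says.** Three places in the protocol article rank the endpoints, and they disagree.

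- **Table 1** (printed within Secondary Outcomes) has the plural heading "Primary outcomes". Under it stand the 56-point skills score and a row for time to critical actions. That row lists three times: to PPV and to CPR (both censored at 900 s), and to scenario completion (censored at 1200 s). Its hypothesis is "Intervention group will have higher hazard of performing critical actions (ie, faster performance) compared to the control group". Its analysis is Cox regression reporting a hazard ratio, 95% CI and P value. The secondary block begins only below this row.
- **Primary Outcome** has a singular heading but mentions the times in passing: "as well as time to critical actions. Therefore, the total maximum score for the primary outcome is 56 points".
- **Data Analysis** names one outcome: "The primary outcome is NR clinical skills performance, assessed at baseline and endline using standardized checklist scores". The times follow in the next paragraph, with the secondary continuous outcomes, and are given no rank.

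Data Analysis sets a two-sided 5% level for every test. Its multiplicity statement reads "Given the exploratory nature of the secondary outcomes, we will not adjust for multiple testing". Sample Size is worked out for the 56-point score alone.

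**The concern.** Which endpoint is primary determines which result the trial is judged on. A reader of Table 1 would count a significant time result as a primary finding. A reader of Data Analysis would not.

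The reason given for not adjusting is that the secondary outcomes are exploratory. That reason cannot cover endpoints that Table 1 calls primary and gives a directional between-group hypothesis. For the primary block as Table 1 draws it, the article states no hierarchy, no requirement that all endpoints succeed, and no split of alpha.

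The timing makes this more pressing. Data collection ended in February 2026 and analysis runs from March to July 2026. If the rank is still open when results are seen, a favourable time result could be presented as primary by citing Table 1, and an unfavourable one set aside by citing Data Analysis.

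**Working it through.** **1. What the sample size covers.** Inputs from Sample Size: difference 11.2, SD 10.3, 80% power, 1:1 allocation, 20% dropout. Data Analysis gives the level as two-sided 0.05.

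- n per group = 2 × (1.960 + 0.842)² × (10.3/11.2)² = 2 × 7.85 × 0.846 = 13.3, rounded up to 14.
- Dropout: 14/0.80 = 17.5, rounded up to 18 per group, 36 in total.

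This reproduces the stated 14, 18 and 36. The calculation is for one endpoint, the score, at 5%. (Sample Size prints the level as 0.05%. Read literally, that would need 32 per group, so 5% was used.)

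**2. How many tests Table 1 implies.** One for the score, plus one Cox model for each listed time, makes 1 + 3 = 4. One model per time is an inference, supported by the separate definitions and the two censoring limits.

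**3. Family-wise error if any one of the four could be claimed.**

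- Independent tests: 1 − 0.95⁴ = 1 − 0.8145 = 0.1855, or 18.5%.
- Upper bound under any dependence: 4 × 0.05 = 20%.
- Correlated tests, by simulation of four normal statistics with an assumed common correlation (1,000,000 draws each):

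| Common correlation | Chance of at least one false positive |
|---|---|
| 0 | 18.6% (simulated) |
| 0.3 | 17.4% |
| 0.5 | 15.6% |
| 0.7 | 13.0% |
| 0.9 | 9.4% |

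- Score as sole primary: 5%.

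The article gives no correlations. All four endpoints come from the same participants and videos, and timing is one of the four global skills inside the score, so some positive correlation is likely.

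**4. What each repair does to the sample size.**

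- Score as sole primary: alpha 0.05, 14 per group, 36 in total. Nothing changes.
- Four primaries with Bonferroni: alpha 0.05/4 = 0.0125. For the score alone, n = 2 × (2.498 + 0.842)² × 0.846 = 18.9, rounded up to 19. Then 19/0.80 = 23.75, rounded up to 24 per group, 48 in total.
- Normal-approximation power for the score at 0.0125: 65% with 14 per group, 78% with 18, 92% with 26 and 97% with 33. The last two correspond to the 66 enrolled, assuming an equal split, with and without 20% loss.

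**The case against.** The strongest reply is that the protocol has one primary outcome and Table 1 merely has a misplaced row. The Aim section ties the primary outcome to clinical skills. The Primary Outcome heading is singular, and the 56 points are 48 + 8 with nothing for times. Data Collection and Integration of Training refers to primary outcome scores. Sample Size rests on the 56-point tool, Randomization and Blinding equates the primary outcome with clinical skills, and Data Analysis names the checklist score. Against these stand one table heading and one loose clause.

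Much of this stands: the weight of the text favours a single primary outcome. It does not remove the contradiction. Table 1 is the article's fullest statement of outcomes, hypotheses and analyses. It also uses clinical skills as a group label over both the score and the time row, so that phrase in other sections does not settle the rank. Nor is this detail left to a separate analysis plan, because the rank is stated here in two incompatible ways.

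Three stronger readings are tempting, and the documents do not support them.

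- A reader might infer that the trial does run four primary tests with an 18.5% error rate. That needs Table 1 to override the other sections, an unstated rule that any one success is enough, and independence.
- A reader might compound this figure with the behaviour of hospital-clustered standard errors when there are only four hospitals. That is a separate question about the Cox models and forms no part of this point.
- A reader might argue that quicker scenario completion could reflect skipped steps. The article does not describe what ends a scenario, so this cannot be shown.

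**Conclusion.** The contradiction holds as written: Table 1 and the Primary Outcome paragraph place the three times with the score, while Data Analysis and Sample Size have the score alone.

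The consequence is conditional. If Table 1 governs and any one success could be claimed, up to four tests at two-sided 5% have no multiplicity rule. Family-wise error is then 18.5% under independence and about 17% to 9% for assumed common correlations of 0.3 to 0.9. If the score is the sole primary outcome, it is 5% and the stated sample size fits. The figures assume one Cox model per listed time and a nominal 5% level for each test.

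The point should be settled before analysis, because it decides which result the trial rests on.

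**What to change.** Before any analysis by allocated group, issue a dated, reasoned amendment that:

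1. names the endline 56-point score, compared by the baseline-adjusted mixed model in Data Analysis, as the sole primary outcome;
2. moves the time-to-critical-actions row of Table 1 to the secondary block and makes the heading singular;
3. rewords the Primary Outcome paragraph so that the times are not part of the primary outcome;
4. updates the registry if its entry follows Table 1.

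If a confirmatory time claim is wanted, prespecify either a hierarchy (for example, one chosen time endpoint tested only after the score is significant) or an alpha split. A Bonferroni split over four endpoints has the power cost shown in the working.

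The single-primary repair needs only rewording; alpha, sample size and the model for the score are unchanged. The price is that time results can no longer be claimed as primary, and that a change of rank made after data collection must be disclosed in the report.
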